### Secondary outcomes

Cardiac dysfunction or remodeling in fetuses from mothers at risk for PE or established PE, defined as abnormal cardiac performance in third trimester echocardiographic ultrasound assessment and/or abnormal cardiac biochemical profile (Copeptin, NT-proBNP, hs-cTnT) in umbilical cord blood at delivery.Abnormal BP or lipid profile in the PE group as compared to the others, in the first, third trimester of pregnancy, or at 12 months after delivery.Development of a combined model for prediction of PE, including biochemical and biophysical markers of CV and placental dysfunction.Cardiac and metabolic status at 12 months after delivery and their correlation with cardiac and PE risk variables obtained during pregnancy. Development of a combined model for prediction of CV risk 12 months after delivery, including biochemical and biophysical markers of CV and placental dysfunction.

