### Secondary aims

To prospectively assess both biochemical and biophysical CV markers in a cohort of patients with risk for PE and in healthy pregnant women, in the first and third trimesters of pregnancy.To determine correlation between angiogenic (PlGF) and anti-angiogenic (sFlt-1) factors in maternal serum, and biochemical and imaging markers of cardiac dysfunction and remodeling in patients with established PE.To evaluate the relationship between placental and maternal cardiac biomarkers and fetal cardiac function in the third trimester of pregnancy.To determine cardiac dysfunction and metabolic status 12 months after delivery in women with PE, and its correlation with CV and PE risk variables obtained during pregnancy.To investigate angiogenesis and CV-related genes in placental samples of women with PE and controls, by microarray and polymerase chain reaction (PCR) validation.To develop a combined model for prediction of cardiovascular risk in PE, that includes placental and cardiac biomarkers, clinical and echocardiographic variables.

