## Outcome measures

### Primary outcome

Maternal cardiac dysfunction or remodeling in the first and third trimesters of pregnancy and 12 months postpartum, defined as any of the following:Abnormal cardiac performance in echocardiographic assessments.Abnormal concentrations of cardiac biomarkers (Copeptin, hs-cTnT, NT-proBNP).

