#### Database development and statistical analysis

A web-based database will be developed through a restricted website. All variables will be recorded, and the collected data will be coded and processed with adequate precautions to ensure patient confidentiality. Each participating physician will receive a login name and password to gain access to the web-secured database, with access restricted to clinicians with electronic password.

Once sample collection and laboratory determinations of biomarkers are finished, we will proceed to evaluation and analysis of the results obtained with the aid of the Statistics Department at our institution. Measures will be normalized to expected values for the respective gestational age. For biomarker measurements without reference values in pregnancy, we will obtain reference values from the control population, estimated by linear modeling and describe as multiples of the median (MoM). Variables not following a Gaussian distribution will be log-transformed for analysis.

For the primary outcome, differences in all registered variables among the three study groups will be evaluated at the three evaluation points. Group comparisons will be performed by analysis of variance (ANOVA), followed by post-hoc tests or Chi-squared tests for proportions. Associations and confusion variables will be explored by a multivariate approach, using logistic regression models.

For secondary outcomes, descriptive data will be analyzed at all relevant time-points, frequency of altered values registered and compared among groups and times. Correlations between biochemical markers, including angiogenic imbalance, and cardiac dysfunction/remodeling will be assessed. Diagnostic test parameters (sensitivity, specificity, positive and negative predictive values) will be calculated, and Cox proportional-hazards model will be performed. Univariate and multivariate analysis will allow identifying which variables can be incorporated to a multivariable model to predict CV risk or disease in PE.

In all analyses, a *p* value below 0.05 will be considered statistically significant. Data will be analyzed using the IBM SPSS Statistics 23 statistical package.

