Some studies have shown that hs-cTn is elevated in pregnant women with hypertension or with PE, compared with healthy pregnancies. These are strong predictors for development of both conditions [37] and are related to mean peak arterial BP in asymptomatic PE patients [38]. Knowing hs-cTn can detect minor myocardial damage like that existing due to ischemia, we shall assess whether PE causes such damage. In addition to hs-cTn, copeptin and natriuretic peptides could be helpful biomarkers for cardiac dysfunction in PE. Copeptin concentrations may be increased in PE, because it is not only a regulator of circulating volume, but also responsive to the CV stress associated with the condition [39]. Volume changes and hemodynamic stress are characteristics of pregnancy that are particularly strong in PE. Santillan [20] was the first to report a high sensitivity and specificity of copeptin to predict PE in the first and second trimesters of pregnancy. A recent meta-analysis has confirmed these findings, extending them to the 3rd trimester, and showing a correlation between copeptin concentrations and PE severity [40]. On other hand, secretion of natriuretic peptides is increased in response to increases in BP, cardiac filling volume, cardiac chamber pressure and dilation [32]; consequently, natriuretic peptide concentrations are increased in PE [41]. We believe NT-proBNP concentrations in pregnant women may be an earlier and alternative tool to echocardiography for detecting cardiac function alterations existing in PE. Our study plans to use all information generated by these biomarkers, along with clinical and echocardiographic variables, to develop a CV risk score during a preeclamptic pregnancy, and at 12 months after delivery.

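### Cardiac biomarkers and echo variables are tested against a dysfunction outcome they help to define: circular at the same visit, and only partly affected in the 12-month model

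*Protocol article*

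**What the plan says.** Under Primary outcome the protocol article sets a composite at three time points: "Maternal cardiac dysfunction or remodeling in the first and third trimesters of pregnancy and 12 months postpartum, defined as any of the following". The first component is "Abnormal cardiac performance in echocardiographic assessments". The second is "Abnormal concentrations of cardiac biomarkers (Copeptin, hs-cTnT, NT-proBNP". Either is enough alone, so a single raised biomarker with a normal echocardiogram makes a woman a case.

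The same markers return as explanatory variables in four places:

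- Database development and statistical analysis, on secondary outcomes: "Correlations between biochemical markers, including angiogenic imbalance, and cardiac dysfunction/remodeling will be assessed".
- The same paragraph: "Diagnostic test parameters (sensitivity, specificity, positive and negative predictive values) will be calculated". No index test, reference standard or visit is attached.
- Secondary aims: a model of cardiovascular risk in preeclampsia "that includes placental and cardiac biomarkers, clinical and echocardiographic variables". Secondary outcomes repeats the plan as "Development of a combined model for prediction of CV risk 12 months after delivery, including biochemical and biophysical markers of CV and placental dysfunction".
- Discussion: the biomarker, clinical and echocardiographic information will be used "to develop a CV risk score during a preeclamptic pregnancy, and at 12 months after delivery".

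The article does not define CV risk separately, and nothing says that a marker under test is removed from the outcome.

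**The concern.** When a test is part of its own reference standard, its accuracy is partly true by definition (incorporation bias). A woman with NT-proBNP above the cut-off is a case because of that value, so NT-proBNP can produce no false positives at that visit, whether or not it says anything about the heart.

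This bears on a question the authors raise. The Discussion suggests that NT-proBNP might show altered cardiac function earlier than echocardiography or in its place. A comparison with echocardiography can answer that. A comparison with an outcome that a raised NT-proBNP satisfies alone cannot. The risk is that a marker with no diagnostic value is reported with perfect specificity and PPV, and that a risk score built from the outcome's own components looks better than it is.

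**Working it through.** The article gives no sensitivity, specificity, AUC or abnormality rate, so there is no figure of its own to reproduce. The structure comes from the text. The rates below are assumptions, chosen to show the effect for a marker that carries no information about echo.

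**1. One marker, same visit, same cut-off.** Let echo be abnormal in e = 20% of women and the marker in q = 10%, independently.

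- Composite prevalence = 1 − (1 − e)(1 − q) = 1 − 0.80 × 0.90 = 0.28.
- Sensitivity against the composite = q / prevalence = 0.10 / 0.28 = 0.357, or 36%.
- Specificity and PPV against the composite = 100%, because every marker-positive woman is a case by definition.
- Against echo alone: sensitivity = q = 10%, specificity = 1 − q = 90%, PPV = e = 20%. These are the values of a useless test.

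Range: with e = 30% and q = 5%, prevalence is 1 − 0.70 × 0.95 = 0.335 and sensitivity 0.05 / 0.335 = 15%. With e = 10% and q = 15%, prevalence is 1 − 0.90 × 0.85 = 0.235 and sensitivity 0.15 / 0.235 = 64%. So over e = 10–30% and q = 5–15%, apparent sensitivity is 15–64%, while sensitivity against echo alone is 5–15%.

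**2. Three markers, same visit.** The outcome lists three biomarkers, so prevalence = 1 − (1 − e)(1 − q)³. At e = 20% and q = 10% this is 1 − 0.80 × 0.729 = 0.417. Any of the three abnormal occurs in 1 − 0.729 = 27.1%, giving an apparent sensitivity of 0.271 / 0.417 = 65%. Over e = 10–30%, apparent sensitivity is 36–63% at q = 5% and 55–79% at q = 10%. In a simulation of 400,000 women per scenario with independent, uninformative markers, the AUC of the highest of the three was 0.68–0.81 (q = 5%) and 0.78–0.89 (q = 10%) against the composite, and 0.50 against echo alone.

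**3. Pregnancy marker, 12-month composite.** The earlier value is no longer part of the outcome. It is linked to it only through the correlation rho between a woman's pregnancy and 12-month values of the same marker. With the same uninformative markers, e = 10–30% and q = 5–10%:

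| rho | AUC against 12-month composite | AUC against 12-month echo |
|---|---|---|
| 0 | 0.50 | 0.50 |
| 0.3 | 0.54–0.58 | 0.50 |
| 0.5 | 0.57–0.64 | 0.50 |
| 0.7 | 0.61–0.73 | 0.50 |

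If 12-month values were themselves predictors (rho = 1), the result would be that of step 2.

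**The case against.** The strongest reply is that the article never states that a component marker will be judged against the composite at the same visit. The diagnostic measures have no named reference standard and may belong to the preeclampsia prediction model, which is also a secondary outcome and is not defined by these markers. CV risk is not expressly equated with the composite. The secondary aims put PlGF and sFlt-1 on one side and cardiac markers on the other, which is not circular. A score calculated during pregnancy may be meant for a later outcome. Echocardiography is recorded separately, so NT-proBNP can be compared with it directly. Details of reference standards may sit in a fuller document.

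Much of this stands, and it limits the point. That the composite is the reference for the diagnostic measures is an inference. A reader might also infer that the accuracy of the 12-month model is wholly built in. The text does not support that: the neighbouring item in Secondary outcomes relates 12-month status to variables obtained in pregnancy, and using an earlier value to predict a later state is legitimate.

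The reply does not remove the correlation statement. It covers biochemical markers including angiogenic imbalance, so not the angiogenic markers alone, and under Biomarker analyses the other assays are hs-cTnT, NT-proBNP and copeptin. Its target is the term that Primary outcome defines. Nor does the reply supply another cardiac outcome: the Discussion expects only subclinical change by 12 months, and the composite is the only maternal cardiac outcome defined. The overlap is fixed in this document, so it is more than omitted detail.

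**Conclusion.** The concern holds in limited form. Followed as written, any same-visit correlation, accuracy measure or risk score that sets copeptin, hs-cTnT, NT-proBNP or an echo variable against the composite is circular. For a biomarker at the cut-off that defines the outcome, specificity and PPV are 100% whatever the marker is worth. The sensitivity inflation (36% against 10% in the example, 15–64% against 5–15% over the range) rests on assumed abnormality rates and on a marker independent of echo.

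The 12-month model is inflated only as far as the same marker persists within a woman. It becomes fully circular only if 12-month values are also entered as predictors, which the sentence describing the model does not exclude because it names no predictor visit.

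A reader might go further and conclude that the primary question is compromised, or that the composite should be kept for description only. Neither follows. sFlt-1 and PlGF are not part of the composite, so relating them to it is not circular, and preeclampsia is not defined by these markers.

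**What to change.** Amend the analysis wording before the data are analysed:

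- Where copeptin, hs-cTnT or NT-proBNP is the correlate, predictor or diagnostic test, use an outcome defined by echocardiography alone.
- Where echo variables are tested against an outcome from the same visit, leave echo out of that outcome. A same-visit score containing both biomarkers and echo would then have no outcome left, so it needs one from a later visit.
- State that predictors of the 12-month model come from pregnancy visits only, and define CV risk at 12 months in line with these rules.
- Name the index test, reference standard and visit for the diagnostic measures.
- Keep the composite for the group comparisons and for the primary question on angiogenic factors.

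No new patients, visits or assays are needed. The cost is fewer events and wider confidence intervals for the accuracy figures. Under the illustrative rates (e = 20%, q = 10%), echo-only cases are 20% of women, against 28% for a composite with one biomarker and 42% with three. The accuracy figures will also look less favourable. Pregnancy echo will still track with 12-month echo. That is legitimate prediction, but should be described as persistence of an abnormality already seen in pregnancy where that is what it is.

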## Statistical analysis

### Sample size

We have planned a 3 year-period recruitment, considering the number of deliveries at our institution. To obtain an adequate sample, a total of 2800 screenings must be performed, assuming there is a 1-to-6 ratio between high-risk cases vs controls. We will include all pregnant women attending our center for first trimester screening and agreeing to participate in the study. They will be divided into two groups according to their PE risk; we plan to include 280 pregnancies with high-risk of PE and 100 patients with low-risk of PE, as well as 60 patients with established PE; we have included an estimated 10% drop-rate during the study. The study has already begun the enrollment; as of 30/09/2021 110 high-risk PE patients, 54 low-risk PE patients and 10 established PE patients have been included.

#### Database development and statistical analysis

A web-based database will be developed through a restricted website. All variables will be recorded, and the collected data will be coded and processed with adequate precautions to ensure patient confidentiality. Each participating physician will receive a login name and password to gain access to the web-secured database, with access restricted to clinicians with electronic password.

Once sample collection and laboratory determinations of biomarkers are finished, we will proceed to evaluation and analysis of the results obtained with the aid of the Statistics Department at our institution. Measures will be normalized to expected values for the respective gestational age. For biomarker measurements without reference values in pregnancy, we will obtain reference values from the control population, estimated by linear modeling and describe as multiples of the median (MoM). Variables not following a Gaussian distribution will be log-transformed for analysis.

For the primary outcome, differences in all registered variables among the three study groups will be evaluated at the three evaluation points. Group comparisons will be performed by analysis of variance (ANOVA), followed by post-hoc tests or Chi-squared tests for proportions. Associations and confusion variables will be explored by a multivariate approach, using logistic regression models.

For secondary outcomes, descriptive data will be analyzed at all relevant time-points, frequency of altered values registered and compared among groups and times. Correlations between biochemical markers, including angiogenic imbalance, and cardiac dysfunction/remodeling will be assessed. Diagnostic test parameters (sensitivity, specificity, positive and negative predictive values) will be calculated, and Cox proportional-hazards model will be performed. Univariate and multivariate analysis will allow identifying which variables can be incorporated to a multivariable model to predict CV risk or disease in PE.

In all analyses, a *p* value below 0.05 will be considered statistically significant. Data will be analyzed using the IBM SPSS Statistics 23 statistical package.

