## Aims

### Primary aim

To determine if a relationship exists between angiogenic environment during pregnancy and the risk of maternal cardiovascular dysfunction and remodeling.

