### Inclusion criteria

Women between 18 and 45 years of age, with singleton pregnancies and high-risk for PE according to our first trimester screening protocol [24], which includes registration/measurement of maternal risk factors, blood pressure (BP), pregnancy-associated plasma protein A (PAPP-A) and mean uterine artery pulsatility index (UtA-PI), at 11^+ 0^ to 13^+ 6^ weeks of gestation. The estimated sample size for the high-risk group is 280 patients, who will be divided according to the subsequent development of PE:True PE: women from the high-risk group who develop PE (estimated *n* = 40)False PE: women from the high-risk group who do not develop PE (estimated *n* = 240)

An additional group of healthy pregnant women with first trimester low-risk screening for PE will be recruited (*n* = 100).

Additionally, women with established diagnosis of PE (*n* = 60) that were not participating previously in the study, will be included at time of diagnosis. The local research coordinator and/or staff will identify eligible women, invite them to participate, provide written and oral information, and obtain the written informed consent.

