#### Biomarker analyses

All blood samples will be collected without anticoagulants. Biomarkers sFlt-1, PlGF, hs-cTnT and NT-proBNP will be measured using automated electrochemiluminescence immunoassays on a Cobas E601 platform (Roche Diagnostics GmbH, Mannheim, Germany). Copeptin will be measured in a KRYPTOR lab instrument by an immunoluminometric assay using two polyclonal antibodies (BRAHMS, Thermo-Fischer, Germany )[21]. The clinical laboratory involved in the study performs standard internal and external quality controls for biomarkers included in the study. For interpreting observed values we will use reference values or ranges obtained in previous studies or recommended guidelines.

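### The analysis assigned to the primary outcome compares preeclampsia-risk groups; the angiogenic exposure named in the primary aim is explicitly tied to cardiac dysfunction only in secondary correlations with no stated adjustment

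*Protocol article*

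**What the plan says.** The Primary aim section sets the question: "To determine if a relationship exists between angiogenic environment during pregnancy and the risk of maternal cardiovascular dysfunction and remodeling". The exposure is angiogenic and the outcome is cardiac.

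The Primary outcome section defines that outcome as a composite: "Maternal cardiac dysfunction or remodeling in the first and third trimesters of pregnancy and 12 months postpartum, defined as any of the following". The components are abnormal echocardiographic performance and abnormal copeptin, hs-cTnT or NT-proBNP. sFlt-1 and PlGF are not components.

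The section on database development and statistical analysis then gives the analysis: "For the primary outcome, differences in all registered variables among the three study groups will be evaluated at the three evaluation points". The tests follow: "Group comparisons will be performed by analysis of variance (ANOVA), followed by post-hoc tests or Chi-squared tests for proportions". The same paragraph ends: "Associations and confusion variables will be explored by a multivariate approach, using logistic regression models".

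The next paragraph, on secondary outcomes, contains the only analysis sentence that puts the two sides of the primary aim together: "Correlations between biochemical markers, including angiogenic imbalance, and cardiac dysfunction/remodeling will be assessed".

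Under Inclusion criteria, risk groups come from a first-trimester protocol "which includes registration/measurement of maternal risk factors, blood pressure (BP), pregnancy-associated plasma protein A (PAPP-A) and mean uterine artery pulsatility index (UtA-PI"). A further 60 women enter on a diagnosis of PE. The angiogenic factors are measured in the study: "Biomarkers sFlt-1, PlGF, hs-cTnT and NT-proBNP will be measured using automated electrochemiluminescence immunoassays".

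**The concern.** The aim asks about one contrast and the stated primary analysis tests another. The group comparison asks whether cardiac measures differ between women classified by PE risk or PE diagnosis. The aim asks whether women with a more anti-angiogenic profile have more cardiac dysfunction.

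The groups are built from blood pressure, maternal risk factors, PAPP-A, uterine artery Doppler and, for one group, PE itself. A significant ANOVA could reflect any of these. A null ANOVA could coexist with a clear angiogenic-cardiac relationship inside the groups. If the text is followed as written, the headline result may not bear on the headline question. The analysis that does would be reported as secondary, with no stated handling of confounding.

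**Working it through.** **1. Aim and analysis side by side**

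| | Primary aim | Analysis stated for the primary outcome |
|---|---|---|
| Explanatory variable | Angiogenic environment | Study group |
| Response | Maternal cardiac dysfunction/remodeling | All registered variables |
| Method | (relationship) | ANOVA or chi-squared; logistic regression with no named exposure |

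Because the response is every registered variable, sFlt-1 and PlGF do enter, but as outcomes of group. Showing that sFlt-1 differs by group and that a cardiac measure differs by group does not show that the two are related within women.

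**2. Can group stand in for the exposure?** Inclusion criteria expect 240 of the 280 high-risk women not to develop PE: 240/280 = 86%, and 240/440 = 55% of the cohort. Neither sFlt-1 nor PlGF is among the listed screening variables. Group is at best an indirect proxy.

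**3. The plan's own figure.** The sizes add up: 280 + 100 + 60 = 440, and 40 + 240 = 280. The article gives no effect size, SD, event rate or power, so 440 cannot be re-derived from a power calculation.

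**4. Illustration of the gap.** Sizes are those planned less the stated 10% loss: low-risk 100 × 0.9 = 90, high-risk 280 × 0.9 = 252, established PE 60 × 0.9 = 54, total 396. The effects below are assumptions and do not come from the article.

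Model, with all noise standard normal:
- exposure x = (group mean of x) + noise
- outcome y = (group mean of y) + b·(x − group mean of x) + √(1 − b²)·noise

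Group means are in SD units, in the order low-risk/high-risk/established PE. Each scenario has 2,000 data sets, tested at 0.05. Monte Carlo standard error near 5% is √(0.05 × 0.95/2000) ≈ 0.5 percentage points.

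| Scenario | Means of x | Means of y | b | ANOVA significant | Pooled correlation, unadjusted | Exposure term adjusted for group |
|---|---|---|---|---|---|---|
| A: no within-group link | 0/0.2/1.0 | 0/0.1/0.6 | 0 | 93.4% | 18.1% | 5.3% |
| B: link, equal outcome means | 0/0.2/1.0 | 0/0/0 | 0.3 | 5.7% | 100% | 100% |
| B2: as B, equal exposure means | 0/0/0 | 0/0/0 | 0.3 | 4.8% | 100% | 100% |

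In A the groups differ in the outcome for other reasons; ANOVA is nearly always significant although there is no within-group relationship. In B and B2 the relationship is present and ANOVA stays at about its nominal 5%. The pooled unadjusted correlation in A is significant in 18% of data sets, more than three times nominal, which is why unstated adjustment matters for the secondary analysis too.

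**5. Feasibility.** Detectable correlation r = tanh[(1.96 + 0.84)/√(n − 3)], two-sided 0.05, assumed 80% power:
- n = 396: r ≈ 0.14
- n = 440: r ≈ 0.13

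This applies to a continuous cardiac measure. Power for the binary composite depends on its frequency, which the article does not give.

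**The case against.** The strongest reply is that the plan already covers the aim. The outcome is binary and the aim speaks of risk, so logistic regression is a natural model. It sits in the primary-outcome paragraph, and the Discussion says that associations between angiogenic factors and cardiovascular findings will be assessed. An unnamed exposure is not an excluded one, and a fuller protocol or SAP may name it. The Background describes PE as a state of angiogenic imbalance, so PE status carries some information on the exposure.

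Much of this stands, and it rules out some stronger readings.
- A reader might infer that the plan never models the angiogenic exposure. The text does not show that, because the logistic regression could include it.
- A reader might infer that the study cannot answer its primary aim. That is true only of the ANOVA/chi-squared comparison taken alone. The correlations are planned, and the Secondary aims add one within established PE.
- A reader might charge the primary analysis with losing information by cutting continuous measures into normal and abnormal. ANOVA uses the continuous values, and the article gives no abnormal rates from which a loss could be computed.

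What does not fall away is the ordering. The article states a specific primary contrast, and it is not the one in the aim. The regression is described as exploratory and names no exposure. The matching analysis is placed under secondary outcomes. This is a stated misalignment, and a SAP that followed the text would carry it forward.

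**Conclusion.** The concern holds as a mismatch between the primary aim and the analysis assigned to the primary outcome. A group difference does not establish a relationship between angiogenic imbalance and maternal cardiac dysfunction, and the absence of one does not exclude it.

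The mismatch itself is read directly from the text and needs no assumption. The percentages (93% with no within-group link; about 5–6% with a within-group r of 0.3 and equal outcome means) depend on assumed effects. They show that the two questions can come apart in either direction; they do not predict this study's results. The judgement also rests on the article alone: a full protocol or SAP that names the angiogenic exposure in the primary model would resolve it.

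**What to change.** Make the primary analysis a logistic regression of the outcome defined under Primary outcome on a gestational-age-adjusted angiogenic measure, for example log sFlt-1/PlGF MoM, taken at the same visit as the outcome or an earlier one. Use the continuous cardiac measures as supporting analyses.

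Adjust for pre-specified confounders available in all groups, such as maternal age, BMI and gestational age at evaluation. Report the estimate with its 95% CI.

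Show the model with and without study group and blood pressure as sensitivity analyses, not as one fixed adjustment. The Discussion proposes that an early anti-angiogenic profile drives remodeling, which then promotes PE, so these variables may be mediators. In addition, no first-trimester study blood pressure is described for the 60 women who join when PE is diagnosed, so it should not be a required covariate.

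Keep the ANOVA and chi-squared group comparisons as supportive.

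The cost is small: some extra analysis and a changed order of analyses. The angiogenic and cardiac measurements are already planned, and MoM conversion and log-transformation are already foreseen in the analysis section.

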**Methods:**

Prospective cohort study of pregnant women with high-risk of PE in first trimester screening, established diagnosis of PE during gestation, and healthy pregnant women (total intended sample size *n* = 440). Placental biochemical and biophysical cardiovascular markers will be assessed in the first and third trimesters of pregnancy, along with maternal echocardiographic parameters. Fetal cardiac function at third trimester of pregnancy will be also evaluated and correlated with maternal variables. Maternal cardiac function assessment will be determined 12 months after delivery, and correlation with CV and PE risk variables obtained during pregnancy will be evaluated.

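### ANOVA for the continuous cardiac variables in groups of 280, 100 and 60 holds its 5% level only if the group variances are similar; Welch's ANOVA would hold it either way

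*Protocol article*

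**What the plan says.** Under Database development and statistical analysis, the Protocol article introduces the primary-outcome analysis by saying that "differences in all registered variables among the three study groups will be evaluated at the three evaluation points". It then names the method: "Group comparisons will be performed by analysis of variance (ANOVA), followed by post-hoc tests or Chi-squared tests for proportions". Significance is a p "value below 0.05 will be considered statistically significant".

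The Sample size section plans "280 pregnancies with high-risk of PE and 100 patients with low-risk of PE, as well as 60 patients with established PE", which adds up to the 440 given in the abstract.

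Two preparatory steps are described before the comparison. Measures are normalised to the values expected for gestational age, with multiples of the median for biomarkers that lack pregnancy reference values. In addition, "Variables not following a Gaussian distribution will be log-transformed for analysis". No step is tied to unequal spread between groups, and no unequal-variance form of ANOVA is named.

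The primary outcome (Outcome measures) is a composite: any echocardiographic abnormality or any abnormal cardiac biomarker. ANOVA therefore applies to the continuous variables behind the composite, and the chi-squared and logistic routes apply to the composite itself.

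**The concern.** The ordinary F test, and post-hoc tests that share its pooled error term, take the group variances to be equal. With balanced groups a departure does little harm. With 280/100/60 it matters, because the pooled error is set mostly by the largest group. If the smallest group has the widest spread, the pooled error understates the uncertainty of that group's mean and the test rejects too often. If the smallest group has the narrowest spread, the test rejects too rarely.

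There is a plausible reason for the PE group to be wider. Women with established PE "will be included at time of diagnosis", so severity at entry is not fixed, and the Discussion cites evidence "showing a correlation between copeptin concentrations and PE severity". Controls are healthy women who screened low-risk. This is an inference, since the article reports no SDs.

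At stake is the validity of each single test, apart from how many tests are run. A difference in spread could be reported as a difference in means, and PE versus control is among the contrasts affected.

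**Working it through.** **Inputs.** From the article: group sizes 280/100/60, sum 440 (agrees with the abstract); three groups; alpha 0.05. Assumed, because the article gives none: the group SDs, with controls set to 1.

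**Baseline.** No power calculation is stated, so the only figure to reproduce is the 5% level. With normal data, equal means, equal SDs and 200,000 simulated trials, the F test rejects at 4.97% (Monte Carlo standard error √(0.05 × 0.95 / 200,000) ≈ 0.0005).

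**Why the level moves.** With equal means but SDs σᵢ, the expected between-group mean square is Σ(1 − nᵢ/N)σᵢ² / 2 and the expected within-group mean square is Σ(nᵢ − 1)σᵢ² / 437. Their ratio should be 1.

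- Equal SDs: (0.364 + 0.773 + 0.864)/2 = 1.00 over 1.00.
- PE SD 1.5: (0.364 + 0.773 + 0.864 × 2.25)/2 = 1.54 over (279 + 99 + 59 × 2.25)/437 = 1.17; ratio 1.32.
- PE SD 2: (0.364 + 0.773 + 0.864 × 4)/2 = 2.30 over (279 + 99 + 59 × 4)/437 = 1.41; ratio 1.63.
- PE SD 0.67: (0.364 + 0.773 + 0.864 × 0.449)/2 = 0.76 over (279 + 99 + 59 × 0.449)/437 = 0.93; ratio 0.82.

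**Simulated rejection of equal means at nominal 5%** (200,000 trials per row):

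| Groups (high-risk / control / PE) | SDs | Ordinary F | Welch |
|---|---|---|---|
| 280/100/60 | 1 / 1 / 0.67 | 3.0% | 5.0% |
| 280/100/60 | 1 / 1 / 1.1 | 5.9% | 5.0% |
| 280/100/60 | 1 / 1 / 1.25 | 7.5% | 5.0% |
| 280/100/60 | 1 / 1 / 1.5 | 10.5% | 5.0% |
| 280/100/60 | 1 / 1 / 2 | 16.0% | 5.0% |
| 252/90/54 (10% loss) | 1 / 1 / 2 | 16.0% | 5.0% |
| 280/100/60 | 1.25 / 1 / 1.5 | 6.5% | 5.0% |
| 280/100/60 | 1.5 / 1 / 2 | 8.1% | 5.0% |
| 240/100/100 (PE cases pooled) | 1 / 1 / 1.5 | 7.9% | 5.0% |
| 240/100/100 (PE cases pooled) | 1 / 1 / 2 | 10.5% | 5.0% |

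The 240/100/100 rows move the 40 high-risk women expected to develop PE (Inclusion criteria) into the PE group: 280 − 40 = 240 and 60 + 40 = 100.

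**PE versus control with the pooled error, unadjusted, checked by hand.** At SDs 1/1/2 the pooled variance is (280 + 100 + 60 × 4)/440 = 1.41. The pooled standard error is √(1.41 × (1/60 + 1/100)) = 0.194, while the true one is √(4/60 + 1/100) = 0.277. The error rate is 2 × [1 − Φ(1.96 × 0.194/0.277)] ≈ 17%; simulation gives 17.1%. At ratio 1.5 simulation gives 11.3%. Coverage of the pooled 95% interval does not depend on the true mean difference, so it would be about 100 − 11.3 = 88.7% and 100 − 17.1 = 82.9%.

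**Cost of Welch if variances are equal.** Simulated power at 280/100/60: 90.5% (ordinary) against 89.9% (Welch) for a PE shift of 0.5 SD, and 73.3% against 72.5% for 0.4 SD.

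**The case against.** **An article condenses the plan.** The text says ANOVA, without specifying the equal-variance form or naming a post-hoc test, and the full plan may already use Welch. That stands as a caveat: if it does, the point is met. But the article does name a method for these variables, the unqualified name ordinarily means the equal-variance test, and the suggestion is a better choice in place of the stated one.

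**The key input is assumed.** This stands. Nothing in the article says PE women are more variable. A reader might infer that false positives will run at two to three times nominal. The documents do not support that: it needs a PE SD roughly 1.5 to 2 times that of both other groups. At 1.1 the rate is 5.9%, and below 1 the test is conservative.

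**The high-risk group may be wider too.** It mixes women who will and will not develop PE. If its SD is 1.25 or 1.5, the rate falls to 6.5% or 8.1%. If only the 40 expected PE cases carry the wider spread and means are equal, its SD is √((240 + 40 × 2.25)/280) = 1.09 or √((240 + 40 × 4)/280) = 1.20, and the rate is 8.9% or 12.5%. The inflation shrinks without vanishing.

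**The plan has safeguards.** Gestational-age normalisation deals with much of the variation from differing time at entry, and a log transformation often evens out spread in skewed biomarkers. Both help. Neither targets severity-related spread, and the log rule is triggered by shape, so a Gaussian echocardiographic variable with unequal variances passes unchanged.

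**The severity evidence points to a mean shift.** True, and where means really differ a false positive is not the issue. The interval for the difference is still too narrow if the PE group is wider.

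**The 280/100/60 layout does not fit every visit.** Women enrolled at diagnosis have no prospective first-trimester assessment. This is correct, so the figures apply to later visits; first-trimester group sizes would differ but would still be unequal.

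**Conclusion.** The point holds in conditional form. Equal-variance ANOVA at 280/100/60 delivers its 5% level only if group variances are similar. Under the assumed SDs examined, the actual level runs from about 3% (PE less variable, ratio 0.67) to about 16% (PE SD twice both others), with about 6.5% to 10.5% in the intermediate cases where the high-risk group is also wider or PE cases are pooled. These figures assume normal data and equal means. The SD ratios are assumptions, and the first data summary by group would show which applies.

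A reader might also infer that the primary outcome itself is tested by an unsound method. It is not: the composite is binary and falls to the chi-squared and logistic analyses. The point concerns the continuous echocardiographic and biomarker comparisons that the article lists under the primary outcome. It is a modest correction that is worth making because it costs almost nothing.

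**What to change.** In Database development and statistical analysis, for continuous group comparisons, replace the ANOVA and unnamed post-hoc tests with: *Welch's ANOVA, followed by Games-Howell post-hoc tests*. Use them by default, not after a preliminary test of variances. Leave the chi-squared tests, the normalisation and the log-transformation rule as they are.

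The cost is one phrase of wording, with no extra data or participants. If variances turn out equal, the power loss is below 1 percentage point (0.6 and 0.8 points in the two cases simulated).
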